#### *Primary and Secondary Outcomes*

The primary outcome will be **clinical malaria**, defined (according to WHO criteria) as parasitemia (malaria parasites detected on a blood smear) of any density plus history of fever (within 48 hours) or axillary temperature  $>37.5^{\circ}\text{C}$ . Criteria for clinical malaria will be taken from the UNICEF Case Management Series, entitled, "Promoting Rational Use of Drugs and Correct Case Management in Basic Health Services – Malaria Prevention and Treatment" published by UNICEF's Programme Division in cooperation with the World Health Organization in 2000. To distinguish unique malaria episodes, treatment will be supervised and follow-up blood smears will be collected from the child as described below in Section 5.2(c).

Secondary outcomes will include: (i) changes in anemia status; (ii) the severity of the clinical malaria (based on level of parasitemia); (iii) cerebral malaria; (iv) hospitalization (from any cause) (v) death; (vi) pneumonia; (vii) diarrhea and dehydration.

*Subjects/study population*

Infants and young children (6-24 months of age), living in the Brong Ahafo Region of northern Ghana, will be included in the study if, at baseline, they are ingesting weaning foods in addition to breastmilk; free from malaria or other major illness; afebrile; living in the study area for the duration of the intervention and follow-up period; and if parental consent is obtained. Inclusion of a child into the study will proceed after the possible risks and benefits are discussed with the parents (in the appropriate local language), and a signed consent is obtained. The exclusion criteria are as follows: severe anemia (hemoglobin <70g/L), weight-for-height <-3 z-score (severe wasting), kwashiorkor (defined as evidence of edema), congenital abnormality, treatment with iron supplements in the past 6 months, or any chronic illness. Children that are severely anemic (Hb<70 g/L) and/or have symptoms of clinical malaria will be excluded from entry to the study and referred to the local health provider for treatment according to Ghana Ministry of Health guidelines.

*Sample Size*

We hypothesize that the incidence of malaria will be significantly higher in children receiving iron versus a placebo of micronutrients without iron. It was decided not to use the change in anemia status as a primary outcome since, in all previous studies with powdered mineral and vitamin fortificants, anemia rates declined compared to placebo controls, or were no different from the improvement in anemia rates observed with iron drops.

Based on the 2006 estimate of “cases and deaths from fevers suspected of being malaria” for children under 5 years of age in all of Ghana (53), the baseline rate of 3.44 episodes/child/year was assumed. We estimated that a total of 351 person-years would be required to detect a 15% increase in malaria incidence rates with 80% power and at a 5% type I error. Based on the experience and expertise of the PI and co-investigator, a difference of 15% in malaria incidence was considered to be clinically significant. Knowing that all children enrolled in the trial will begin the 5-month intervention period at a similar risk level, and accounting for 15% loss to follow-up, as well as the need to test the hypothesis twice (due to the interim analysis by the Data Safety and Monitoring committee), the sample size has been calculated as 1940 children per seasonal cohort (970 per group), or a total of 3880 subjects (see Table 1 below). All calculations were reviewed by 2 statisticians who will be involved in subsequent analyses.

Table 1: Sample size calculation adjusted for testing the hypothesis twice

| Least Meaningful Difference | 2006 rates  | Adjustment for use of bed-net | Rate unexposed | Rate exposed | Person-years | Follow-up years | n          | Loss to follow-up | Sample size per group* |
|-----------------------------|-------------|-------------------------------|----------------|--------------|--------------|-----------------|------------|-------------------|------------------------|
| 0.05                        | 3.44        | 0.75                          | 2.58           | 2.71         | 3017         | 0.42            | 7240       | 0.15              | 8326                   |
| 0.1                         | 3.44        | 0.75                          | 2.58           | 2.84         | 772          | 0.42            | 1854       | 0.15              | 2132                   |
| 0.15                 | 3.44 | 0.75                   | 2.58    | 2.97  | 351   | 0.42     | 843 | 0.15       | 970             |
| 0.2                         | 3.44        | 0.75                          | 2.58           | 3.10         | 202          | 0.42            | 485        | 0.15              | 558                    |

\*Adjusted for estimated bed net use and loss to follow-up

**5.2 Procedures***Recruitment, Randomization Process and Blinding*

Subjects will be recruited from villages in the Kintampo Health Research Centre (KHRC) study area once permission has been obtained from the village assemblies and elders, as well as the parent or guardian of the eligible child. Field researchers, employed by the KHRC, will visit individual households/compounds and interview parents or caregivers regarding the inclusion criteria. Once consent has been obtained and documented via signature or thumbprint, eligible children (one per household/compound) will be enrolled and randomized, using a computer-generated model, to either the iron (Fe) or placebo (P) group.

Sachets containing the powdered minerals with and without iron will look and taste identical with the exception that each package will be marked with an 'A' or 'B' denoting packages with or without iron. The study team and caretakers of children will be blinded to the 'A' or 'B' designation. Only the manufacturer of the powdered fortificant (in Ghana) and a research pharmacist each in Toronto and Kintampo will hold the key to the randomization and 'sachet' code lists. The key will be revealed to the 'Data and Safety Monitoring Committee (DSMC)' at the end of the first phase if a significant difference in outcomes is observed, and to the researchers after the database is closed and statistical analyses completed.

*Supply and content of the powdered mineral and vitamin fortificant.*

The applicant (SZ) has extensive experience with the powdered mineral and vitamin product both in research protocol and in working with governments, UN agencies and NGOs for scaling up the intervention. The product will be procured from a production facility in Canada, India or Bangladesh. Each of these facilities has supplied a reliable high quality product to the applicant for past research projects. The production facilities in India and Bangladesh are UNICEF approved facilities. The dose of micronutrients including iron is shown in Table 2 below. The dose of individual nutrients is based on WHO or IOM-DRI guidelines, or estimates based on these guidelines.

Table 2: Justification of a powdered mineral and vitamin supplement dose for infants and young children

|                       | 6-11 mo          |                      | 12-24 mo |         | Powdered fortificant |
|-----------------------|------------------|----------------------|----------|---------|------------------------------------|
|                       | WHO  | IOM DRI  | WHO      | IOM DRI |                                    |
| Vitamin A, µg RE      | 400              | 500*                 | 400      | 300     | 400                                |
| Vitamin C, mg         | 30               | 50*                  | 30       | 15      | 30                                 |
| Folic Acid, µg        | 80               | 80*                  | 160      | 150     | OMIT                               |
| Iron, mg  | 9.3              | 11                   | 5.8      | 7       | 12.5                               |
| Zinc mg   | 4.1              | 3                    | 1.1      | 3       | 5                                  |

 Recommended Nutrient Intakes. Source: Joint FAO/WHO Expert Consultation. (2002) Vitamin and mineral requirements in human nutrition. World Health Organization, Geneva, Switzerland.

 Recommended Dietary Allowances (RDA). Sources: Institute of Medicine, Dietary Reference Intakes. National Academy Press, Washington D.C.

 The dose of 12.5 mg is the current INACG/WHO/UNICEF recommendation for children 6-24 months of age for large scale distribution. It assumes a medium bioavailability (5-10%).

 Assuming moderate bioavailability (30%)

\* Based on Adequate Intake (AI) estimates

*Clinical protocol*

a) *Baseline:* After consent is provided, subjects will be screened for anemia (based on hemoglobin) and parasitemia. Enough blood will be taken to determine ferritin (SF), C-reactive protein (CRP), serum transferrin receptor (TfR) and zinc protoporphyrin (ZnPP). Those who are severely anemic (Hb <70 g/L), or have clinical signs of infection (including malaria) will be referred to the study clinician who will offer the child the standard care, as defined by the Ghana Ministry of Health. All other children will be enrolled and randomized to either the iron (Fe) or placebo (P) group. The child's weight and length measurements will be recorded, as well as any relevant demographic (age, gender) and historical health information (birth weight, immunization status, and previous hospitalizations). Caregivers will also be asked to provide information regarding their usual feeding practices and health-seeking behaviours. All households will be provided with a treated bed net and a supply of powdered fortificant with oral instructions on how to use each.

*b) Monitoring visits:* Field researchers will visit each subject at their home every week in the first month of the study and at 4 week intervals for the next 4 months. At each visit, the field researcher will conduct a health assessment (including axillary temperature) and collect information on feeding history, supplement compliance, bed net use and morbidity. At the initial weekly visits, 7 new sachets will be provided, and then at the start of the second month, 30 new sachets will be provided to last for a month. Clear instructions for storage and administration of sachets will be provided to families. All used and unused sachets will be counted and recorded. It has been our experience in other similar studies in Ghana and elsewhere that by providing pre-emptive information on the impact of the fortificant to parents (like telling parents that stools will darken from the iron, and that children will become more active and have enhanced appetites), the adherence to the use of the sachets is generally in the range of 70 – 98%. We will provide this pre-emptive information in the current study.

*(c) Tracking the subjects:* All subjects who become ill and need to visit a health facility will be identified and tracked through their study identity cards. The use of such cards is standard practice at the Kintampo Health Research Centre (KHRC). If a fever has been reported or recorded, a blood sample will be taken to determine parasite species and count. If the child is admitted to the hospital or health centre, blood parasite level will similarly be determined, and further tests will be conducted (as needed) to rule out cerebral malaria, pneumonia, diarrhea, and/or dehydration. All treatments will follow the treatment guidelines in Ghana (Ghana Ministry of Health). For those assessed to have malaria, the first-line antimalarial (Artesunate-Amodiaquine) will be prescribed and provided. To determine if the treatment has been successful, and from the perspective of the study, to distinguish unique malaria episodes, treatment will be supervised and follow-up blood smears will be collected from the child on the 3rd, 7th, 14th and 28th day following treatment (this process has been successfully used in past trials including “A multi-centre, randomized, double-blind, double dummy study comparing the efficacy and safety of chlorproguanil-dapsone-artesunate versus artemether-lumefantrine in the treatment of acute uncomplicated *Plasmodium falciparum* malaria in children and adolescents in Africa Protocol #: SB-714703/005. Collaborations among KHRC/LSHTM/GSK/MMV/WHO”). All slides (with thick and thin films) will be stained with Giemsa following fixing of the thin film and read twice by independent microscopists blinded to each other’s reading. A third microscopist will be asked to read the slide if there is disagreement between the first two. The readings will be used to determine if the treatment has been successful or not.

*c) Follow up:* At the end of 5 months, subjects will again be screened for anemia, ferritin, CRP, serum transferrin receptor, zinc protoporphyrin and a blood smear for their malaria status. The subjects will be weighed and measured, and caregivers will again be asked about feeding history, supplement use, and bed net use. Any remaining sachets will be collected and counted. All families that have completed the intervention will be provided with a study closure package (including some rice and soap) as has been the standard goodwill practice of KHRC to participants from the communities. For those children who are anemic, based on their end-line hemoglobin assessment, an additional 60 sachets of iron-containing powdered fortificant will be provided. Providing iron to anemic children is not a safety issue in this case because they will be eligible for treatment according to the WHO statement on the use of iron in malaria endemic areas (3).

*d) Discontinuation of supplementation.* Supplementation will be stopped if any of the following is reported: admission to the hospital ward for >5 days; evidence of chronic diarrhea (defined as loose stools lasting >4 weeks); prolonged fever of unknown origin; emergence of any exclusion criteria after randomization. Prompt, daily disclosure by field workers of any concerns will be encouraged. If necessary, children will be referred to local physicians for treatment according to local standards. Reasons for stopping supplementation voluntarily will be recorded.

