## **KHRC Priority Research Areas**

- Communicable diseases (CDs), particularly Malaria, TB and HIV/AIDS
- Sexual and Reproductive Health
- Maternal, Neonatal and Child Health
- Mental Health
- Non-communicable diseases (NCDs) such as hypertension and cancer
- Health Systems
- Using the DSS to track progress towards the Millennium Development Goals (MDGs) using indicators such as mortality levels, patterns and trends

Since 2003, [name] and his research teams at KHRC have characterized the epidemiology of malaria in the Kintampo area in the middle belt of Ghana (49-51). He has documented the incidence of malaria in children less than 5 years in this area as 7 attacks per child per year ([name] et al., in press). The transmission levels have been high throughout the year with an average inoculation rate of 269 infective bites per person per year ([name] et al., in press). [name] and his team of researchers are documenting the manifestations (both clinical and laboratory indicators) of severe and complicated malaria. Several antimalarials have been tested and evaluated in this area (52) and currently the most advanced malaria vaccine is being tested in Kintampo as one of several African countries. For more details on the KHRC laboratory and clinical facilities, please see pages 22-23 of this application (Resources Format Page).

The Kintampo Health Research Centre (KHRC) was awarded the 2008 Prince of Asturias Award for International Cooperation in recognition of its contribution to the fight against malaria in sub-Saharan Africa. The Prince of Asturias Foundation was formed by His Royal Highness, the Prince of Asturias, heir to the throne of Spain. It has conferred its awards since 1981. The awards are intended to acknowledge scientific, technical, cultural, social and humanitarian work carried out internationally by individuals, groups or in the categories of communication and humanities, social sciences, arts, letters, scientific and technical research, international cooperation, concord and sports.

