## 5. RESEARCH DESIGN AND METHODS

### 5.1 Design Conceptual or Clinical Framework

#### *Study Design*

The proposed study is a community-based blinded randomized controlled trial with 2 study arms that will be conducted in two phases:

- Phase I will take place during the dry season (December to April), when malaria transmission rates are lower. Eligible subjects (one per household) will be individually randomized to receive a daily dose of either a powdered vitamin/mineral fortificant containing 12.5 mg of iron (plus ascorbic acid, vitamin A and zinc), or a placebo (containing all micronutrients excluding iron), added to complementary foods, for 5 months.
- Phase II will take place during the wet season (June to October), when malaria transmission rates are higher. Eligible subjects, who did not participate in Phase I, will be individually randomized to one of the two study arms as described above and followed for 5 months.

A dual phase design, with two unique cohorts, was chosen so that preliminary results (at the end of phase 1) could be assessed by an independent Data Safety and Monitoring Committee. It is possible that during the dry season no impact of iron will be detected, while during the wet season, an impact will be observed. With this possible outcome, it is potentially feasible to translate this knowledge into a Ministry of Health Program to only provide iron supplementation (fortification) during the dry months of the year (December to April).

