## 8. PROTECTION OF HUMAN SUBJECTS

### 8.1 Risks to Human Subjects

#### 8.1a Human Subjects Involvement and Characteristics

- Proposed involvement of human subjects
  - i. Studies using animals are not appropriate to answer the research questions posed in this proposal, namely to determine the impact of the provision of iron on the susceptibility to clinical malaria among infants and young children (6-24 months of age)

living in a high malaria burden area, using a powdered vitamin and mineral 'sprinkle' added to complementary foods.

- Characteristics of the subject population – number, age range, health status
  - i. Number: Approximately 930 in the intervention group and 930 in the control group
  - ii. Age: 6 – 24 months
  - iii. Health Status – generally healthy
- Inclusion/exclusion criteria for any subpopulation
  - i. Children to be included must meet the criteria described above. They must be free of clinical signs of infection (including malaria) at the time of enrolment. They must have plans to remain in the study area for the duration of the intervention. Informed consent must be freely given by a parent of the children enrolled for the study. Both boys and girls will be recruited without bias. Girl children will specifically be encouraged to participate, as appropriate.
  - ii. Children will be excluded if they fail to meet the inclusion criteria shown above.
- Rationale for involvement of special classes of subjects (e.g. children)
  - i. The highest malaria burden is in children in the first 3-4 years of life and the highest iron deficiency anemia burden is in the age range 6 – 24 months of age. Thus, we choose to include children who are at highest risk of anemia and malaria.
- List any collaborating sites where human subjects research will be performed, describe role of those sites and collaborating investigators in performing proposed research
  - i. The research field work will be conducted in northern Ghana, within the catchment area of the Kintampo Health Research Centre (KHRC). KHRC is one of three Ministry of Health Research Centres in Ghana.
  - ii. Research Ethics Board approval will be from two sources: the University of Toronto, the home institution of the PI and the Ghana Ministry of Health.
  - iii. The University of Toronto, Hospital for Sick Children PI will provide oversight of the project, while the co-investigator at KHRC will supervise all aspects of the field research.

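### The sample-size text calls 351 person-years a total at 5%, but Table 1 shows it is per group at 2.5% per test; Section 8.1a's 930 + 930 children matches neither one cohort nor the trial

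*Protocol*

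**What the plan says.** Protocol Section 5.1, under Sample Size: "We estimated that a total of 351 person-years would be required" for a 15% rise in the malaria rate, "with 80% power and at a 5% type I error". The next sentences bring in 15% loss to follow-up and the need to test the hypothesis twice because of the interim analysis. They arrive at "1940 children per seasonal cohort (970 per group), or a total of 3880 subjects".

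Table 1 is titled "Sample size calculation adjusted for testing the hypothesis twice". Its 15% row runs: rates 2.58 and 2.97 per year, 351 person-years, 0.42 year of follow-up, n of 843, 15% loss, and 970 in a last column headed as the sample size per group. The table prints no significance level and does not say whether the test is one- or two-sided.

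Section 8.1a, in the human-subjects part, gives the number of children as "Approximately 930 in the intervention group and 930 in the control group". It does not say whether this is per cohort or for the whole trial.

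**The concern.** Two sets of printed figures do not agree with each other.

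The first is the description of 351. The prose presents it as the requirement for the whole comparison, at an unadjusted 5%, with the adjustment for two tests still to come. If Table 1 already holds a per-group figure at an adjusted level, a statistician working from the prose cannot rebuild the table. That reader would not know the level for each test and could apply the adjustment a second time. The level matters because the interim test, at the end of the first cohort, carries a stopping rule (Section 5.5).

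The second is the number of children. Section 8.1a tells the ethics boards how many children will be exposed to a possible malaria risk, and it should match the enrolment plan.

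**Working it through.** **Inputs (Section 5.1 and Table 1).** Baseline rate 3.44 × 0.75 = 2.58 per child-year. Exposed rate 2.58 × 1.15 = 2.967 (printed as 2.97). Power 80% (z = 0.842). Follow-up 5/12 year. Loss 15%.

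**Formula, two Poisson rates.** Person-years per group = (z_α + 0.842)² × (r0 + r1) / (r1 − r0)².

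For the 15% row, (r0 + r1) / (r1 − r0)² = 5.547 / 0.387² = 37.04.

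- Two-sided 2.5% (z = 2.241): 3.083² × 37.04 = 352.0 per group. The plan prints 351.
- Two-sided 5% (z = 1.960): 2.802² × 37.04 = 290.7 per group, or 581 in both groups.
- One-sided 5%: 229 per group, or 458 in both groups.
- Two-sided 2.94%: 338 per group.

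The other rows agree:

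| Increase | Table 1 person-years | Two-sided 2.5%, per group | Two-sided 5%, per group |
|---|---|---|---|
| 5% | 3017 | 3021 | 2495 |
| 10% | 772 | 774 | 639 |
| 15% | 351 | 352 | 291 |
| 20% | 202 | 203 | 167 |

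All four rows match at two-sided 2.5% per group to within 0.3%. Log-ratio and square-root versions of the formula differ by less than 1 person-year. With the rounded rate 2.97, the 15% row gives 346.8 at 2.5% and 286.4 at 5%, so the conclusion is the same.

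**Per group or total.** 351 / (5/12) = 842.4, printed as 843, which becomes 970 per group. So 351 is per group, and one cohort needs 2 × 351 = 702.

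**If the prose order is followed literally.** Adjusting 351 for two tests as a further step would give 351 × 352.0 / 290.7 = 425 person-years, a figure that appears nowhere in the plan.

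**Loss to follow-up.** Every row uses n × 1.15: 7240 gives 8326, 1854 gives 2132, 843 gives 970 (969.5 rounded up) and 485 gives 558. Allowing for 15% loss would be 843 / 0.85 = 992, or 22 more per group (2.3%). Power with 970 per group, at two-sided 2.5%, is Φ[0.387 / √(5.547 / PY) − 2.241]:

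- Lost children contribute no follow-up: PY = 970 × 0.85 × 5/12 = 343.5, power 78.9%.
- Dropout is uniform over the five months (an assumption): PY = 970 × 0.925 × 5/12 = 373.9, power 82.5%.

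**Number of children.** Section 8.1a: 930 + 930 = 1,860. Section 5.1: 970 + 970 = 1,940 per cohort, × 2 = 3,880.

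- Read as the whole trial: 1,860 / 3,880 = 48%, short by 2,020.
- Read as one cohort: 930 against 970 per group, 40 / 970 = 4.1% low, and the second cohort is not mentioned.

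**The case against.** The strongest reply is that nothing operational depends on the faulty sentence. Section 5.1 and Table 1 both state 970 per group, and enrolment follows that number. This stands. It also disposes of a reading that some may draw, that the trial has only 351 person-years in all. That would be 175.5 per group, with power of 59% at 5% or 47% at 2.5%, but nobody plans such a trial.

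Second, 5% is coherent as the overall error split over two tests, and the table title supports that. So one should not say that the 5% is simply false. What remains is that the prose attaches 5% to 351 and puts the adjustment afterwards. The 2.5% is inferred from the table, not printed in it.

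Third, the loss formula is a small matter. The outcome is analysed as events in person-time, so children who leave part-way still contribute, and under uniform dropout power is above 80%. This stands too.

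A reader might also infer that 80% power cannot hold in both seasons, because one rate serves both cohorts while the dry season is described as the period "when malaria transmission rates are lower". The protocol does not support that. It discloses the planning rate as a national 2006 figure and gives no dry-season rate. Section 4 says transmission at the site has been high throughout the year, and it reports the "incidence of malaria in children less than 5 years in this area as 7 attacks per child per year". Half of that figure after the bed-net factor, 7 × 0.75 × 0.5 = 2.63, still exceeds the planned 2.58.

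Finally, the shortfall of 2,020 children holds only if 930 means per arm over both cohorts. Section 8.1a does not say which is meant, so both readings have to be given. Neither agrees with Section 5.1.

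**Conclusion.** The point holds as a correction of printed figures, not as a fault in the design. The 351 person-years is a per-group figure for each cohort and already includes the adjustment for two tests, at two-sided 2.5% per test. The prose describes it as a total at 5%. This rests on the table's own rates and 80% power; of the levels tried, only two-sided 2.5% per group fits the rows.

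The count in Section 8.1a conflicts with Section 5.1 on either reading: about half the trial, or 4% low with one cohort left out. It carries the most weight, because it sits where the ethics boards look for the number of children.

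The loss convention is minor. It moves power to between about 79% and 82.5%, depending on how much follow-up lost children contribute, and does not call for a larger sample.

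**What to change.** - Section 5.1: replace the sentence with 351 person-years per group per cohort (702 per cohort), 80% power, two-sided 2.5% per test, as reproduced from Table 1 (overall 5% over two tests). Remove testing twice from the list of later adjustments, since 351 already contains it. The sponsor's statisticians should confirm the inferred 2.5%.
- Table 1: label the person-years and n columns as per group and print the significance level.
- Section 8.1a: give 970 per group per cohort, 1,940 per cohort and 3,880 in all, and notify both ethics boards.
- Loss to follow-up: keep 970. Add a note that loss was applied as n × 1.15, and that power is about 79% if lost children contribute no follow-up and 82.5% if dropout is uniform.

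The cost is text and table edits and one notice to the ethics boards. No additional children, and no change to the analysis or the timetable.

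### Table 1 allows for 15% loss to follow-up by multiplying by 1.15 instead of dividing by 0.85, so 970 per group leaves 824.5 completing children, not the 843 required (minor)

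*Protocol*

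**What the plan says.** Section 5.1 (Sample Size) gives the requirement and the final number:

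- "We estimated that a total of 351 person-years would be required to detect a 15% increase in malaria incidence rates with 80% power". The text calls this a total, but Table 1 uses it as the figure for one group.
- The error level beside it is "with 80% power and at a 5% type I error", while the table is headed "Table 1: Sample size calculation adjusted for testing the hypothesis twice".
- The enrolment target is "the sample size has been calculated as 1940 children per seasonal cohort (970 per group), or a total of 3880 subjects", reached after "accounting for 15% loss to follow-up".

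In the row for a 15% increase, Table 1 shows 351 person-years, 0.42 years of follow-up, n = 843, a loss of 0.15 and a final 970 per group. The footnote to the last column reads "Adjusted for estimated bed net use and loss to follow-up". The bed-net factor of 0.75 has already been applied to the rate (3.44 to 2.58), so the loss allowance is the only step between n and the last column. The protocol does not write out the formula for that step.

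**The concern.** A loss rate of 15% applies to the children enrolled. To finish with n children, the trial must enrol n/0.85. Adding 15% of n to n gives a smaller number, and the stated loss then takes the completers below n. The three figures in the selected row (843 needed, 15% lost, 970 enrolled) cannot all hold.

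At stake is whether the stated power follows from the stated loss rate. The section says that two statisticians reviewed all the calculations, so readers will take the table as it stands.

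**Working it through.** **Inputs.** From section 5.1 and Table 1: baseline rate 3.44 episodes per child-year, bed-net factor 0.75, effect of 15%, 80% power, 5 months of follow-up, 15% loss.

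- Unexposed rate: 3.44 × 0.75 = 2.58
- Exposed rate: 2.58 × 1.15 = 2.967
- Difference 0.387, sum 5.547

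**1. Reproducing the 351 person-years.** For two Poisson rates, person-years per group = (z_alpha + z_power)² × (r1 + r2) / (r1 − r2)².

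- Two-sided 2.5%: (2.241 + 0.842)² × 5.547 / 0.387² = 352.0. Two variants of the formula (log rate ratio and square root) give 352.6 and 351.6.
- Two-sided 5%: about 291.

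The table's 351 therefore matches a two-sided 2.5% level per test, which agrees with its heading about testing twice. The protocol does not state that level; it is inferred from this match.

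**2. Reproducing n.** 351 / (5/12) = 842.4, shown as 843. This step gives every child the full 5 months.

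**3. Reproducing the last column.**

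| Difference | n | n × 1.15 | Table 1 | n / 0.85, rounded up |
|---|---|---|---|---|
| 5% | 7240 | 8326.0 | 8326 | 8518 |
| 10% | 1854 | 2132.1 | 2132 | 2182 |
| 15% | 843 | 969.45 | 970 | 992 |
| 20% | 485 | 557.75 | 558 | 571 |

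Every row follows the factor 1.15. (The 970 is what results if n is carried unrounded at slightly above 843.) No row is near division by 0.85.

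**4. What 970 delivers.**

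- Completers after 15% loss: 970 × 0.85 = 824.5, which is 18.5 below 843.
- Loss that 970 covers: 1 − 843/970 = 13.1%.
- Enrolment for 15% loss: 843/0.85 = 991.8, so 992 per group, 1984 per cohort and 3968 in all. That is 22 more per group (2.3%) and 88 more overall.

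**5. Person-years and power per cohort.** Power = Φ(0.387 / √(5.547/PY) − 2.241), at two-sided 2.5%. The 15% lost are 970 × 0.15 = 145.5 children.

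| Time contributed by lost children | Person-years per group | Power |
|---|---|---|
| None | 824.5 × 5/12 = 343.5 | 78.9% |
| A quarter of 5 months | (824.5 + 36.4) × 5/12 = 358.7 | 80.8% |
| Half of 5 months | (824.5 + 72.75) × 5/12 = 373.9 | 82.5% |
| Table 1 target | 351 | 79.9% |

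Break-even: (842.4 − 824.5) / 145.5 = 12.3% of the 5 months, about 19 days. If lost children stay longer than that on average, the 351 person-years are met.

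**The case against.** The strongest reply is that children are the wrong unit to count. The outcome is an incidence rate, summarised over person-time (section 5.5), compared by Poisson regression and analysed by intention to treat in all randomised children. Section 5.2 plans home visits every week in the first month and every 4 weeks after that, so time before loss would be observed. A child who leaves after more than about 19 days already contributes enough, on average, to close the gap. This stands as far as person-years and power go, and it makes that part of the point conditional. It does not rescue the table, which converts person-years to children at full follow-up, then inflates the number of children, and says nothing of partial time. The protocol does not say when losses are expected.

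A second reply is that the effect is small beside other planning inputs. That is also fair. Section 4 reports 7 attacks per child-year locally, against the 3.44 assumed. With the same bed-net factor, the rates would be 5.25 and 6.04, and 343.5 person-years would give about 98% power. Over-dispersion, which section 5.5 says will be checked, would lower power.

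A reader might infer that the trial is underpowered, or that enrolment must rise to 992. The documents do not support either. Even in the worst case for lost follow-up, the cost is about one point of power at two-sided 2.5%. At the two-sided 5% level that could be read from the text, 343.5 person-years would give about 86%.

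**Conclusion.** The arithmetic error is established from the protocol's own figures: the factor is 1.15 in all four rows, 970 less 15% leaves 824.5 completers instead of 843, and 970 covers a 13.1% loss.

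The shortfall in person-years (343.5 against 351) and in power (78.9% against 79.9%) is not established without condition. It needs two assumptions: that lost children contribute no time, and that each test is at two-sided 2.5%. Above an average contribution of about 12% of follow-up, it disappears.

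The power figures refer to detecting the 15% increase for which Table 1 plans. They do not describe the comparison with the 10% tolerance limit in section 5.5, which is a separate question. The point is minor.

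**What to change.** Keep enrolment at 970 per group and correct the statement. Either of these would do:

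- Say that 970 per group gives about 80% power with up to 13% loss, or about 79% if 15% of children contribute no follow-up, at two-sided 2.5% per test.
- Say that the partial person-time of lost children is counted, give the assumed average contribution, and show the calculation.

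Then treat all four rows of Table 1 in the same way. One option is to show the values from division by 0.85 (8518, 2182, 992, 571) with a note that 970 is the number to be enrolled. The other is to keep the present last column and relabel the loss column as the loss that the factor 1.15 covers, which is 13%.

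The cost is a sentence or two and a few table entries. Recruitment, conduct and analysis do not change. If the power is restated without counting partial person-time, the stated power or the stated loss becomes slightly less favourable.
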